[figure not shown]

| Name of Active Ingredient:
benfluorex
(S00780)                                                                                                                                                                                                                                                                                                                                                                                                                                                                                                                                                                                                                                                                                                                                                                                     | Page:                                                   |                                          |
| Title of study: A one-year multicentre, international, randomised, double-blind study with comparison of benfluorex (150 mg bid or 150 mg tid) versus pioglitazone (30 mg od or 45 mg od) in combination with sulfonylurea administered orally for the treatment of type 2 diabetes.
Protocol N°: CL3-00780-148                                                                                                                                                                                                                                                                                                                                                                                                                                                                                                                                     |                                                                |                                          |
| International coordinator: [name], MD, PhD
Service d'Endocrinologie - Unité 11
Hôpital Cardio-Vasculaire et Pneumologie Louis Pradel
[name]
[name] – FRANCE                                                                                                                                                                                                                                                                                                                                                                                                                                                                                                                                                                                                            |                                                                |                                          |
| Study centre:
Multicentre study performed in 5 countries (France, Argentina, Germany, India, South Africa). The recruitment of patients will be competitive whatever the country.                                                                                                                                                                                                                                                                                                                                                                                                                                                                                                                                                                                                                                                                   |                                                                |                                          |
| Study period:
- Study duration for the participant: 1 year + run-in (4 weeks)
- Study completion date: 1 st February 2008                                                                                                                                                                                                                                                                                                                                                                                                                                                                                                                                                                                                                                                                                                             |                                                                | Study development phase: III      |
| Objectives: The primary objective is to demonstrate the non-inferiority of the combination benfluorex plus sulfonylurea compared to the combination pioglitazone plus sulfonylurea on the evolution of HbA1c (main criterion) over one year of treatment. Both benfluorex and pioglitazone will be administered at optimal dosage for the treatment of type 2 diabetic patients insufficiently controlled on sulfonylurea monotherapy.
The secondary objective is to demonstrate the superiority of benfluorex combined with sulfonylurea compared to pioglitazone combined with sulfonylurea on Low Density Lipoprotein (LDL) cholesterol level.
The other secondary objectives are to assess the efficacy on Fasting Plasma Glucose (FPG), the safety profile, the cardiovascular risk profile and the economic balance of the two treatments. |                                                                |                                          |
| Methodology:
- randomised (by IVRS), double-blind, double-dummy, parallel group, comparative (benfluorex versus pioglitazone) study,
- with stratification at baseline on country and HbA1c $\leq 8\%$ or $> 8\%$ .                                                                                                                                                                                                                                                                                                                                                                                                                                                                                                                                                                                                                              |                                                                |                                          |
| Number of participants:
Planned: 950 patients analysed in the Full Analysis Set (475 by group), 1000 included with at least 500 patients with baseline HbA1c $> 8\%$ .                                                                                                                                                                                                                                                                                                                                                                                                                                                                                                                                                                                                                                                                              |                                                                |                                          |
| Diagnosis and main criteria for inclusion:
Out-patients with type 2 diabetes diagnosed according to WHO criteria, male or female aged $\geq 35$ years and $\leq 80$ years, BMI between 25 and 40 kg/m  (inclusive), treated in monotherapy with a sulfonylurea at stable dose for at least 3 consecutive months prior to the selection visit and at dose $\geq 50\%$ of the maximal recommended one with a percentage of HbA1c $> 7\%$ and $\leq 10\%$ as measured by High Performance Liquid Chromatography (HPLC) in a central laboratory.                                                                                                                                                                                                                                                                                            |                                                                |                                          |
| Study drug: Benfluorex (S00780) administered orally at the daily doses of 150 mg (dose I), then 300 mg (dose A) or 450 mg (dose B).
Benfluorex will start at inclusion visit (W0) at 150 mg. The dose will be increased in all the patients from 150 mg to 300 mg two weeks after W0 visit. At W8, possibility to increase the dose to 450 mg to obtain FPG level below 7.8 mmol/L. From W16 until W52, dose level adapted to obtain an HbA1c level $< 6.5\%$ (all measurements performed by central laboratory within 7 days before the visit). Possibility to decrease the study dose at any moment in case of safety issue.
During the whole study, all patients will maintain unchanged the dose of their usual sulfonylurea treatment except in case of severe or repeated hypoglycaemia.                                                   |                                                                |                                          |

|                                                                                              |                                                                        |                                              |
|----------------------------------------------------------------------------------------------|------------------------------------------------------------------------|----------------------------------------------|
| Name of the sponsor: I.R.I.S.
[name]
[name] - FRANCE | Individual Study Table
Referring to Part
of the Dossier | (For National Authority Use
only) |
| Name of Finished Product:
Trade Name (specify the country)                        | Volume:                                                         |                                              |
| Name of Active Ingredient:
benfluorex
(S00780)                                | Page:                                                           |                                              |

**Comparator:** Pioglitazone administered orally at the daily doses of 30 mg (dose A) or 45 mg (dose B). Pioglitazone will start at W0 at 30 mg, with the possibility to increase the dose to 45 mg at W8 to obtain FPG level below 7.8 mmol/L. From W16 to W52, dose level adapted to obtain an HbA1c level < 6.5% (all measurements performed by central laboratory within 7 days before the visit). Possibility to decrease the study dose at any moment in case of safety issue. During the whole study, all patients will maintain unchanged the dose of their usual sulfonylurea treatment except in case of severe or repeated hypoglycaemia.

**Duration of treatment:** a 52-week double-blind comparative study preceded by a 4- week placebo run-in period.

**Criteria for evaluation:**  
(Central laboratory for all biological parameters).  
EFFICACY MEASUREMENTS:  
**Primary efficacy criterion:** HbA1c (%) at each visit (W0, W4, W8, W16, W28, W40 and W52).  
**Secondary efficacy criteria:**

- LDL cholesterol at each visit.
- FPG at each visit.
- Fasting plasma insulin at W0 and W52 visit (HOMA-IR).
- Other fasting serum lipids:
  - total cholesterol, High Density Lipoprotein (HDL) cholesterol and triglycerides at each visit.
  - Non-HDL cholesterol, Apo A1, Apo B at W0, W28 and W52 visit and LDL particle size (optional) at W0 and W52 visit.
- High sensitive C Reactive Protein (hsCRP) at W0, W40 and W52 visit.
- Waist circumference at W0, W28 and W52 visit.

SAFETY MEASUREMENTS:

- Recording of adverse events (including hypoglycaemia) at each visit.
- Follow-up of cardiovascular events at each visit (Adjudication Committee).
- Centralised biochemistry (including lactic acid assessment at W0 and W52) at W0, W28 and W52 visit.
- Liver parameters follow-up (focusing on ALAT) at W0, W4, W8, W16, W28, W40 and W52 visit.
- Haematology tests at each visit with haemoglobin and haematocrit follow-up.
- NT-proBNP at W0, W028 and W52.
- Physical examination (sitting blood pressure, heart rate, body weight) at each visit.
- Echocardiography (with centralized reading) and 12- lead ECG performed at W0, W52 and in case of suspicion of heart failure.

OTHER:

- Serum library taken at W0 and W52 will be kept at the central laboratory in order to perform further tests in diabetes (no genetic test), its complication markers and safety issues if necessary.
- Economic balance.

**Statistical methods:**  
Efficacy analysis:  
**Primary efficacy criterion: HbA1c (%)**  
Main analytical approach: change from baseline to the last post-baseline value  
The main analysis will test the non-inferiority of benfluorex to pioglitazone on the change from baseline value to last post-baseline value using a general linear model studying treatment effect with baseline and country as covariates. The non-inferiority limit will be set at 0.4%.  
**Other efficacy criteria** will be analysed with the same model.

|                                                                                                          |                                                                                    |                                          |
|----------------------------------------------------------------------------------------------------------|------------------------------------------------------------------------------------|------------------------------------------|
| Name of the sponsor: I.R.I.S.
[name]
[name] - FRANCE | Individual Study Table
Referring to Part
of the Dossier | (For National Authority Use only) |
| Name of Finished Product:
Trade Name (specify the country)                              | Volume:                                                                     |                                          |
| Name of Active Ingredient:
benfluorex
(S00780)                                | Page:                                                                       |                                          |

Safety analysis:

Descriptive statistics will be provided for adverse events (including cardiovascular events and oedemas), episodes of hypoglycaemia, laboratory tests, vital signs (blood pressure, heart rate, weight), ECG and echocardiography abnormalities.

Other analysis: Economic balance.

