### 9.6. Participant withdrawal criteria

#### 9.6.1. Withdrawal criteria

Premature discontinuation of treatment, does not necessarily mean that the patient prematurely stops the participation in the study. Information to be collected during the follow-up of these participants is given in section 9.6.2. These follow-up modalities are used to insure the efficacy and safety evaluation of all patients who received the study drug.

The reasons for premature discontinuation of treatment are:

- **Adverse events or any condition incompatible with continuation of either treatment** according to the judgement of the investigator or for which the continuation of the study is recommended (refer to the investigator's brochure of benfluorex and pioglitazone monography in appendices 5 and 6). These include:
  - **Hypoglycaemia incompatible with treatment continuation**, e.g. occurrence of one episode of severe hypoglycaemia or repeated non severe hypoglycaemia (> 3 per month) if the sulfonylurea dose can not be decreased anymore.
  - **ALAT increase > 3 times the ULN value**, after 2 consecutive tests performed in 7 days apart (see appendix 5).
  - **Cardiac failure** (see appendix 10).
  - **Clinically significant anaemia** defined by an haemoglobin level < 12g/dL in men and < 11g/dL in women and a decrease  $\geq 1.5$  g/dL in men and  $\geq 1$  g/dL in women (see appendix 12).

- **Major deviation to protocol incompatible with continuation of either treatment** (including pregnancy).
- **Treatment failure (lack of efficacy) defined as uncontrolled metabolic state with:**
  - **HbA1c > 9.5% at W16 or HbA1c > 9% at W28 or W40** unless increase to dose level B is still possible. If external factors (poor compliance, change of diet and lifestyle, occurrence of infectious or inflammatory disease, intake of corticosteroids) are detected, the investigator will reinforce diet advice and recommendations about treatment intake and/or study protocol compliance. At the following study visit, if the HbA1c is still > 9% the study treatment will be stopped.
  - **or hyperglycaemia** unexplained by external factors and confirmed by either:
    - o clinical symptoms (thirst, polyuria,...) and FPG  $\geq$  13.9 mmol/L
    - o or no symptom and FPG  $\geq$  13.9 mmol/L at 2 consecutive measurements separated by an interval of 2 to 4 weeks.
- **Any medical event requiring administration of an unauthorised concomitant treatment** (see paragraph 10.3).

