### **14.1.4. Statistical methodology**

#### Study Outcome

Characteristics of patients including demography, prognostic factors, baseline values of assessment criteria will be described by treatment group and overall for the RS.

Treatment duration, duration of exposure to treatment, global treatment compliance (test drugs and sulfonylurea), status of patients and reason for withdrawal, protocol deviations, concomitant treatments will be described by treatment group and overall for the RS.

Main characteristics of patients will also be described for the SS, the FAS and the PPS.

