#### Safety

Safety analyses will be carried out on the Safety Set.

- Adverse events

Number of adverse events, number and percentage of patients reporting at least one adverse event will be described by System Organ Class and Preferred Term, by treatment group and overall. The same analysis will be performed for emergent adverse events and serious adverse events.

- Hypoglycaemia, oedema and cardiovascular events:

A survival analysis will be performed in case of sufficient number of events.

- Clinical laboratory evaluation

Laboratory parameters will be described by group for the safety set using value at the visit, last value under treatment and change from baseline to last value under treatment.

Moreover, biochemistry and haematology parameters will be classified according to the laboratory reference ranges and alert values for the potentially clinically significant abnormal values, and shift tables from baseline to first event will be presented.

- Vital signs

Vital signs will be described by group using value at the visit, last post-baseline value and change between baseline and last post-baseline value.

Moreover, blood pressure and heart rate will be classified according to the abnormal low and high values.

- ECG

ECG abnormalities will be described.

- Echocardiography

Centralised LVEF will be described by group using value at the visit, last post-baseline value and change between baseline and last post-baseline value. Moreover centralised echocardiography abnormalities will be described.

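### All, emergent and serious adverse events are tabulated only as crude counts and percentages, although treatment stops can leave the two arms with unequal time at risk

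*Protocol*

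**What the plan says.** **Safety summaries.** The synopsis (Statistical methods, Safety analysis) says: "Descriptive statistics will be provided for adverse events (including cardiovascular events and oedemas), episodes of hypoglycaemia", followed by laboratory tests, vital signs, ECG and echocardiography. It does not say which statistics. Section 14.1.4, Safety, does so for adverse events: "Number of adverse events, number and percentage of patients reporting at least one adverse event will be described", by class and term and by arm, and it repeats this for emergent and for serious events. The population is fixed: "Safety analyses will be carried out on the Safety Set".

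Hypoglycaemia, oedema and cardiovascular events have their own entry in 14.1.4: "A survival analysis will be performed in case of sufficient number of events". No number is given for what is sufficient.

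**Exposure.** Under Study Outcome, 14.1.4 has this described by arm: "Treatment duration, duration of exposure to treatment, global treatment compliance". Nothing links exposure to the event tables.

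**Stopping.** Section 9.6.1 stops treatment for lack of efficacy at "HbA1c > 9.5% at W16 or HbA1c > 9% at W28 or W40", unless a step to dose level B remains open, or for marked hyperglycaemia "unexplained by external factors and confirmed by either" of two glucose criteria. It also stops treatment for safety, for example "Hypoglycaemia incompatible with treatment continuation", a confirmed ALAT rise, cardiac failure or anaemia.

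**After stopping.** Sections 8.2.1 and 9.6.1 say that stopping treatment need not end participation, and both refer to 9.6.2 for what is then collected. Section 9.6.2 lists data for a withdrawal visit, plus the outcome of adverse events that led to withdrawal. Appendix 10 adds one check two weeks after confirmed heart failure. No further scheduled visits are set out.

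**The concern.** A count, or a percentage with at least one event, depends on how long patients are watched as well as on the event rate. If one arm has more early stops and little is recorded afterwards, two drugs with the same true rate will give fewer events and a lower percentage in that arm.

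Comparing the safety profiles is part of the study purpose (section 7), and these tables are where it will be read. Describing exposure in a separate table lets a reader notice an imbalance but does not correct the event figures for it.

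**Working it through.** The protocol gives no figure for this point: no expected share of treatment failures and no event rate. The stop shares below are assumptions. The follow-up of 52 weeks and the visit weeks come from section 8.2.1.

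**Model.** The event hazard is constant and equal in both arms. A share f of an arm stops at week w and is not observed afterwards.

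- Mean exposure per patient, in units of the 52-week period: E(f, w) = (1 − f) + f × w/52.
- Ratio of expected counts, arm with more stops to arm with fewer: E(f1, w) / E(f2, w).
- Share with at least one event, for one-year risk p and h = −ln(1 − p): (1 − f)p + f(1 − exp(−h × w/52)).

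**Counts.** For 10% v 5% stopped at W16: (0.90 + 0.10 × 16/52) / (0.95 + 0.05 × 16/52) = 0.931/0.965 = 0.964. Likewise:

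| Stopped | all at W16 | all at W28 | all at W40 |
|---|---|---|---|
| 10% v 5% | 0.964 | 0.976 | 0.988 |
| 15% v 5% | 0.928 | 0.953 | 0.977 |
| 25% v 5% | 0.857 | 0.906 | 0.953 |

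A difference of 5 to 10 points lowers counts by 1.2% (1 − 0.988) to 7.2% (1 − 0.928). The 20-point row is an extreme case.

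**Percentages.** Appendix 5 (section 4.8) reports oedema in 6–9% of pioglitazone patients over one year, so take p = 8%, and p = 30% for a commoner event. With 15% v 5% stopped at W16:

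- p = 8%: 7.2% v 7.7%.
- p = 30%: 27.1% v 29.0%.

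**Is 5 to 10 points plausible?** As a rough check, assume normally distributed HbA1c with SD 1.5% (section 14.2 gives this SD for the change) and shift the mean by the whole 0.4% margin. From an assumed mean of 7.5%, the share above 9.5% goes from P(Z > 2.0/1.5) = 9.1% to P(Z > 1.6/1.5) = 14.3%, a gap of about 5 points. The largest gap at any threshold is 2Φ(0.2/1.5) − 1 = 10.6 points. A difference such as 5% v 30% does not fit a drug that is within the margin.

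**What rates do.** Under this model, events divided by exposure return the same hazard in both arms, a ratio of 1.00. If instead all events fall before W16, the crude percentages are already equal, and dividing by total exposure inflates the rate in the arm with more stops: by 0.965/0.896 = 1.08 for 15% v 5% at W16.

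**The case against.** **The statistical analysis plan may add rates.** It is not shown, and exposure-adjusted columns are often left to it. This stands as far as it goes: the absence of rates is not an error in the protocol. But 14.1.4 does name a measure for these tables, 14.1 has the later plan follow the protocol's principal features, and nothing requires rates.

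**The events of most interest already have a time-based method.** A reader of the synopsis alone might infer that hypoglycaemia, oedema and cardiovascular events are only counted. The documents do not support that, since 14.1.4 plans a survival analysis, and censoring deals with unequal follow-up. Nor do they say that it is limited to first events. What remains is that it is conditional on an unstated number of events and does not reach the general, emergent and serious event tables.

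**Observation may continue after stopping.** Sections 8.2.1 and 9.6.1 allow it, and 12.3.1.3 requires notification for 30 days after the final visit, and later if the event is likely due to the research. That covers only events needing immediate notification, and 9.6.2 sets no later visits, so equal observation is possible but not secured.

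**Rates can mislead too.** This stands. Appendix 5 (section 4.8) describes visual disturbance on pioglitazone as mainly early, and for such events the crude percentage is the better guide. Rates should not be the sole basis for comparing the arms.

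**Conclusion.** The point holds as a cheap improvement to the stated method. For all, emergent and serious adverse events, the protocol's named measure takes no account of time at risk, while its own stopping rules can make time at risk unequal. Crude figures then understate events in whichever arm loses more patients.

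The size is modest: roughly 1% to 7% of counts for a 5 to 10 point difference in stops. This assumes the stop shares, a constant and equal hazard, all stops at one visit and no observation afterwards. Later stops or continued follow-up make it smaller.

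A reader might go further and infer that the less effective drug will look safer. The documents do not support that. They give no failure rates, and the safety stops in 9.6.1 shorten observation in the less safe arm, which may or may not be the less effective one. The net direction is unknown.

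**What to change.** In section 14.1.4, Safety, with a matching line in the synopsis:

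- For the emergent and serious adverse event, oedema and cardiovascular event tables, add the number of patients with a first event per 100 patient-years at risk.
- For hypoglycaemia, add the number of episodes per 100 patient-years of exposure.
- Keep the crude counts and percentages beside the rates, and state that the two are read together.

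The cost is a wording change and a few extra columns. Duration of exposure is already planned under Study Outcome for the Randomised Set; the rates need the same quantity for the Safety Set. No visit, procedure or clinical rule changes. The downside is the assumption of a roughly constant hazard, which is why the percentages stay for events that cluster early.
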